12.2. Analysis set

The analysis set will consist of the group of all eligible subjects receiving part or all of the protocol treatment.

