# Schema

Follow-up period: 3 years after enrollment of the last subject

Outcome reporting: from discontinuation / completion of the protocol treatment to 3 years after enrollment of the last subject

Perform curative therapy

Squamous cell cancer of the head and neck

(Maxillary sinus, oral cavity, oropharynx, hypopharynx, larynx)

Stage III or Stage IV A or B

Capable of undergoing curative therapy

Test arm: 250 subjects

TS-1 80, 100, 120 mg/day

2 weeks on, 1 week off for 1 year

Control arm: 250 subjects

UFT 300, 400 mg/day

Daily administration for 1 year

Enrollment

(Enrollment period: April 2006 to March 2009)

Informed consent

Confirm tumor-free

(Within 3 months of completion of curative therapy)

Randomization

Adjustment factors (site, stage, type of curative therapy, study site)

Summary of study design

∙Phase: III ∙Randomization: yes (minimization)

∙Design features: 2-arm parallel design ∙Level of blinding: open-label

∙Type of control: active control (UFT)

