# Eligibility Criteria

5.1. Inclusion criteria

Patients satisfying all of the following conditions at consent will be enrolled in the study.

1) Can be enrolled within 3 months after completion of first curative therapy

2) Histological diagnosis of squamous cell cancer

3) Primary site is the maxillary sinus, oral cavity, oropharynx, hypopharynx, or larynx (except T3N0 of the glottis)

4) Clinical or pathological Stage III or Stage IVA or IVB that has undergone first curative therapy (surgery or radiotherapy (including combination chemotherapy and radiotherapy)

Subjects will be excluded if they have lower Level IV (supraclavicular fossa) or Level V metastases pretreatment or in resected specimens.

5) Tumor eradication (primary tumor and lymph node metastases) is confirmed within 3 months of completion of first curative therapy (refer to “5.3. Definition of tumor eradication by curative therapy”).

6) Did not receive antineoplastic therapy between the completion of the first curative therapy and study enrollment.

7) 20 to 75 years of age at consent

8) Performance status (PS) of 0 or 1

9) Capable of taking oral medications.

10) Has the following levels of bone marrow, hepatic, and renal function within 14 days prior to study enrollment.

| WBC | ≥ 3,500 /mm^3^, < 12,000 /mm^3^ |
| --- | --- |
| Neut | ≥ 2,000 /mm^3^ |
| PLT | ≥ 100,000 /mm^3^ |
| Hb | ≥ 9.0 g/dL |
| T.Bil | < 1.5 mg/dL |
| AST∙ALT | < 100 IU/L |
| Cr | < 1.2 mg/dL |

11) Has not had multiple primary cancers within the last 3 years

12) Has personally given written informed consent.

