6.1. Randomization method and randomization adjustment factors

Subjects will be randomized to the test arm (TS-1-treated arm) or control arm (UFT-treated arm). Randomization will be performed by the minimization method, using the 4 factors of (1) primary disease site, (2) stage (III, IVA, IVB), (3) type of curative therapy (surgery or radiotherapy), and (4) study site.

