# Treatment Plan

7.1. Protocol treatment

After completion of enrollment with the Data Center, the test treatment (TS-1) or the control treatment (UFT) will be started within 3 months after completion of curative therapy. The protocol treatment will in principle be performed on an outpatient basis.

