7.4. Follow-up at discontinuation of protocol treatment

Except for the subjects listed below, every effort will be made to follow-up for survival, metastasis, and relapse all of the subjects who discontinued the protocol treatment, based on the provisions in 7.3. If metastasis or relapse is confirmed, only outcome will be followed up.

1) The subject died.

2) The subject withdrew consent to be followed up.

3) The subject was found to be ineligible after beginning the protocol treatment.

4) Follow-up was compromised for some other reason.

Follow-up after treatment discontinuation will be performed every 3-6 months, counting from the starting day of the protocol treatment.

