11.1. Primary endpoint

Disease-free survival (DFS)

The period from the enrollment date to earliest date among the date that relapse was diagnosed, date that secondary cancer was diagnosed, and date of death from any cause. For survivors not diagnosed with relapse or secondary cancer, DFS will be cut off at the last survival confirmation date.

Definition of relapse and secondary cancer

∙Definition of relapse and relapse confirmation date

“Relapse” will be diagnosed when any of the following criteria apply.

(1) Findings on diagnostic imaging (simple chest radiography, ultrasonography, CT, MRI, PET, etc.) that are not secondary cancer will be considered “relapse.” When relapse is diagnosed by multiple diagnostic methods, the date of the earliest test will be considered the “relapse confirmation date.”

(2) When relapse is diagnosed by pathological tests (cytology, biopsy), the date of the earliest test will be considered the “relapse confirmation date.”

(3) An increase in tumor markers will not be considered “relapse.”

∙Definition of secondary cancer (double cancer, multiple cancer) and secondary cancer confirmation date

(1) Definition of secondary cancer

Findings satisfying all of the criteria below from Warren and Gates Diagnostic Criteria 1) will be considered “secondary cancer.”

(1) Each of the tumors exhibits clear malignancy.

(2) Each of the tumors is separate and distinct.

(3) One tumor is not a metastasis of the other.

(2) Definition of secondary cancer confirmation date

(1) When there are findings on diagnostic imaging (simple chest radiography, ultrasonography, CT, MRI, PET, etc.), the date of the imaging will be considered the “confirmation date” and when secondary cancer is diagnosed by multiple diagnostic methods, the date of the earliest test will be considered the “secondary cancer confirmation date.”

(2) When secondary cancer is diagnosed by pathological tests (cytology, biopsy), the date of the earliest test will be considered the “confirmation date.”

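### The single analysis set in 12.2 drops randomized subjects who never start treatment or are later ruled ineligible, which can bias an open-label superiority comparison timed from enrollment

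*Protocol*

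**What the plan says.** Protocol section 12.2 consists of one sentence: "The analysis set will consist of the group of all eligible subjects receiving part or all of the protocol treatment". No other set is defined, so it governs both the time-to-event analyses (12.3.1) and the adverse event comparison (12.3.2).

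The endpoint clock starts earlier than membership of that set. Section 11.1 defines DFS as "The period from the enrollment date to earliest date among the date that relapse was diagnosed", with secondary cancer and death from any cause as the other events. RFS and OS in 11.2 also start at enrollment. The Schema states "Level of blinding: open-label".

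Treatment follows enrollment (7.1), and section 7.3 lists ineligibility discovered after enrollment as a reason to stop treatment. Section 7.4 then exempts certain subjects from the general duty to follow for survival, metastasis and relapse. Its third exception reads "The subject was found to be ineligible after beginning the protocol treatment". Visits after discontinuation are scheduled "counting from the starting day of the protocol treatment", and sections 9.1.3 and 9.2 use the same anchor.

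**The concern.** Randomization makes the arms comparable at enrollment. Section 12.2 then imposes two conditions that can be settled afterwards: that a dose was taken, and that eligibility still stands. A subject who relapses, dies or declines the allocated drug before the first dose leaves the analysis, and any event already counted by the endpoint definition goes too.

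Eligibility is partly a matter of judgement. Tumor eradication after curative therapy (5.1, 5.3) is the clearest example: an early relapse could be reread as residual disease at entry, which would turn a primary event into an exclusion. The protocol does not require such rulings to be made without knowledge of arm and outcome, or from pre-randomization data only.

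If exclusions differ between arms and relate to prognosis, the hazard ratio moves away from the truth in either direction. Because outcomes for some excluded subjects need not be collected, an all-randomized analysis added later might have to censor them and assume that this is uninformative.

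A smaller consequence concerns safety. A treated subject later ruled ineligible is also outside the set used to compare adverse events.

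**Working it through.** **1. Clock against membership**

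| Item | Fixed when | Section |
|---|---|---|
| Arm | Enrollment | 6, 6.1 |
| Start of DFS, RFS, OS | Enrollment | 11.1, 11.2 |
| At least one dose taken | After enrollment | 7.1, 12.2 |
| Eligibility still upheld | Possibly after enrollment | 7.3 item 8, 12.2 |
| Anchor for follow-up visits | First dose | 7.4, 9.1.3, 9.2 |

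**2. The plan's sample size (12.1)**

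Inputs: 3-year DFS 50% on UFT, HR 0.7, 3 years' accrual, 3 years' follow-up, two-sided α 0.05, power 80%. I assume exponential DFS and uniform accrual.

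- Hazards: ln 2 / 3 = 0.231 per year (UFT) and 0.7 × 0.231 = 0.162 (TS-1). 0.5^0.7 = 61.6%, as stated.
- Event probability: 1 − (e^(−3λ) − e^(−6λ)) / (3λ) = 0.639 (UFT) and 0.512 (TS-1).
- Schoenfeld events: 4 × (1.960 + 0.842)² / (ln 0.7)² = 247. Then 247 / (0.639 + 0.512) gives 215 per arm.
- Freedman: 253 events, 220 per arm.

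The stated 216 is reproduced. The further 250 − 216 = 34 subjects per arm are not linked in the text to ineligible or untreated subjects.

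**3. Power is not the difficulty**

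With all 500 analysed, events = 250 × 1.1516 = 288. Power = Φ(√288/2 × 0.357 − 1.960) = 85.7% (Freedman 85.0%). With 10% excluded it is 81.9%, and with 15% excluded 79.7%.

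**4. Possible bias, on assumed inputs**

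The documents give no exclusion rates, so these inputs are mine: no true effect, 250 per arm, hazard 0.231 per year, 15% of each arm at 2 or 3 times that hazard, and all exclusions taken from that high-risk group. Each row summarizes 6,000 simulated trials per hazard multiple (Cox HR, two-sided log-rank test).

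| Excluded TS-1 / UFT | Mean HR | Type I error |
|---|---|---|
| 6% / 2% | 0.96-0.98 | about 5% |
| 8% / 3% | 0.96-0.97 | about 6% |
| 10% / 2% | 0.93-0.95 | about 7-10% |
| 3% / 2% | 0.99 | 4-5% |
| 2% / 2% or 3% / 3% | 1.00 | 4-5% |

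In every scenario the all-randomized analysis gave HR 1.00 with error at or slightly below 5%.

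Hand check of the 10%/2% row: the high-risk share left is 5/90 = 5.6% on TS-1 and 13/98 = 13.3% on UFT. At twice the hazard, the ratio of mean hazards at time zero is 1.056/1.133 = 0.93. At three times it is 1.111/1.265 = 0.88. The ratio drifts towards 1 as high-risk subjects have their events, which fits the simulated averages of 0.95 and 0.93.

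Reversing the exclusion rates reverses the direction. At 2%/6% the HR would be about 1/0.98 to 1/0.96, or 1.02 to 1.04.

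**The case against.** The strongest defence is that the set is close to everyone who was eligible and treated. One dose keeps a subject in, so toxicity during treatment cannot remove anyone. Only refusal or an event before the first dose can, and the protocol neither compares TS-1 and UFT toxicity nor shows that refusal would differ by arm. Events before the first dose should be few: at 0.231 per year, an assumed gap of 2 to 4 weeks gives 250 × 0.231 × 2/52 = 2.2 to 250 × 0.231 × 4/52 = 4.4 per arm. Eligibility criteria are mostly baseline facts recorded at central enrollment. All of this stands, and it limits the likely size. It does not justify the rule, because whether exclusions are few and balanced is unknown until the data are in.

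Three stronger readings are tempting and are not supported:

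- *An intention-to-treat analysis is ruled out for good.* The third exception in 7.4 lifts a duty for one subgroup and does not forbid collecting outcomes. On never-treated subjects the protocol is silent. Sections 9.1.3 and 10.2 also contain assessments tied to the calendar, at 3 and 5 years after the last enrollment, which need no first dose. An unseen analysis plan might add an all-randomized set. What remains is that outcomes may be incomplete.
- *Exclusions are decided by people who know the arm.* The protocol does not say who rules on late ineligibility or what they know. The defect is that it sets no safeguard.
- *The two time limits create untreated subjects.* Section 5.1 accepts a subject who "Can be enrolled within 3 months after completion of first curative therapy", while 7.1 says treatment "will be started within 3 months after completion of curative therapy". Late enrollment leaves little time to start, but both limits can be met, nothing says a late starter goes untreated, and any effect would apply to both arms.

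**Conclusion.** The point holds. The only analysis set in this protocol allows post-randomization exclusions from a superiority comparison timed from enrollment, in an open-label trial with no blinded eligibility review, and the follow-up rules may leave gaps in an all-randomized analysis.

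The likely size is modest and cannot be derived from the documents. On the assumptions above, moderate imbalance shifts a null HR by 2-4 points with type I error of about 5-6%. A marked imbalance of 10% against 2% shifts it by 5-7 points with error of about 7-10%. Equal or nearly equal exclusion does essentially no harm. These shifts are small beside the design HR of 0.7, but would matter for a borderline result.

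A reader might infer that the comparison is biased in favour of TS-1. The documents do not show this: bias needs exclusions that are both unequal and related to prognosis, and it could run either way.

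**What to change.** **Section 12.2.** Make all randomized subjects, analysed as allocated, the primary set for DFS, RFS and OS. Keep the present set as a sensitivity analysis. Use all treated subjects for adverse events.

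**Section 7.4, with 9.1.3 and 9.2.** Delete the third exception, and count outcome follow-up from enrollment for every randomized subject, including those never treated, unless consent to follow-up is withdrawn.

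**Sections 5.1 and 7.1.** As a side matter, reconcile the enrollment and treatment-start windows.

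**Cost.** Protocol wording, and outcome follow-up of a few more subjects. Including untreated and ineligible subjects may dilute the effect slightly. The 85% power found above is before any such dilution, and no additional subjects are needed on the plan's own assumptions.

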12.3. Analysis items and methods

12.3.1. Disease-free survival, overall survival, and relapse-free survival

Disease-free survival, overall survival, and relapse-free survival curves will be estimated by the Kaplan-Meier method. The stratified log-rank test, stratified by randomization adjustment factors, except for study site, will be used for between-group comparisons. To estimate the therapeutic effect, the Cox proportional hazards model will be used to find the hazards ratio of the therapeutic effects and its 95% confidence interval.

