4.2. Staging

UICC TNM Version 6 will be used.

The staging table is shown below.

| Stage | T | N | M |
| --- | --- | --- | --- |
| Stage 0 | Tis | N0 | M0 |
| Stage I | T1 | N0 | M0 |
| Stage II | T2 | N0 | M0 |
| Stage III | T3 | N0, N1 | M0 |
|  | T1, T2 | N1 | M0 |
| Stage IV A | T1, T2, T3 | N2 | M0 |
|  | T4a | N0, N1, N2 | M0 |
| Stage IV B | T4b | Any N | M0 |
|  | Any T | N3 | M0 |
| Stage IV C | Any T & N | | M1 |

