# Observations, Tests, Reported Parameters, and Schedule

9.1. Observation and test parameters, and treatment information to be reported

9.1.1. Before enrollment (confirmation of eligibility) and baseline parameters

1) Information obtained before enrollment (entered in the enrollment form)

Basic patient information

Date of birth, age at consent (can be automatically calculated from date of birth and date of consent), sex, height at consent, weight at consent, body surface area at consent (can be automatically calculated from height and weight), date of written informed consent

Information on disease to be treated

Histological diagnosis: Squamous cell cancer

Primary site: Maxillary sinus, oral cavity, oropharynx, hypopharynx, larynx (except T3N0 of the glottis)

Baseline Stage: III, IVA, IVB

TNM staging: T(1, 2, 3, 4a, 4b), N(0, 1, 2, 3), M(0)

Curative therapy information

First curative therapy: surgery (date of surgery), radiotherapy (radiation duration and total dose), completion date of first curative therapy

Other concomitant therapy: Yes / No (If “Yes,” surgery, radiotherapy, chemotherapy [fluoropyrimidines, platinating agents, other ]),

Tumor eradication confirmation date, means of tumor eradication confirmation (diagnostic imaging, histopathology, cytology)

ECOG performance status scale: PS (0, 1)

Clinical laboratory tests (Test results obtained within 14 days before enrollment will be used.)

Test date

Hematology: WBC, Neut, PLT, Hb

Blood biochemistry: T.Bil, AST (GOT), ALT (GPT), Cr, albumin*, LDH*, ALP*, Na*,

K*, Ca*, CRP* Parameters marked with an asterisk will be entered into the baseline report.

Current medical history: Presence of infections, presence of gastrointestinal disorders, presence of interstitial pneumonia and/or pulmonary fibrosis, presence of diabetes mellitus, presence of heart disease, presence of hepatic disorders, presence of diarrhea (watery stools)

2) Baseline information (to be entered into the baseline report)

Recent cancer history: Presence of previous disease, diagnosis, year of diagnosis

Concurrent / previous disease besides cancer: Diabetes mellitus, hypertension, hyperlipidemia, coronary artery disease, stroke, other

Signs and symptoms (The highest grade in the 14 days before beginning the protocol treatment will be confirmed.):

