# Statistical Considerations

12.1. Rationale for target sample size

The results of large-scale comparative studies in Western countries were used as the rationale for the disease-free survival rate in the control arm. This was done because there are no reports of Japanese studies in which UFT treatment was performed on control subjects as in the present study that could be evaluated.

The 3-year disease-free survival rate among subjects that had undergone curative therapy for Stage III, IVA, and IVB squamous cell cancers of the head and neck was approximately 35-45% in subjects that received radiotherapy postoperatively and approximately 40-59% in subjects that received combination radiotherapy and chemotherapy postoperatively.

From these results, it was hypothesized that the 3-year disease-free survival rate would be 50% in the control (UFT) arm. Thus, 216 subjects per arm would be required to have a hazard ratio of 0.7 (3-year disease-free survival rate: 61.6%) for the test (TS-1) arm versus the control arm with an enrollment period of 3 years, follow-up period of 3 years, two-sided α of 0.05, and statistical power of 80%. A sample size of 250 subjects per arm (500 in both arms) was selected because a power of test of at least 80% could be guaranteed with 250 subjects per arm.

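### The planned stratified log-rank test is valid and adequately powered, but it leaves performance status and N category, both recorded before randomization, unused; adjusting for them could add 0 to 5 points of power.

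*Protocol*

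**What the plan says.** Section 12.3.1 sets one between-group test for DFS, RFS and OS: "The stratified log-rank test, stratified by randomization adjustment factors, except for study site, will be used for between-group comparisons". For the effect size it says that "the Cox proportional hazards model will be used to find the hazards ratio of the therapeutic effects and its 95% confidence interval", and names neither covariates nor strata for that model.

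Section 6.1 lists the minimization factors: "1) primary disease site, (2) stage (III, IVA, IVB), (3) type of curative therapy (surgery or radiotherapy), and (4) study site". With study site dropped, three remain. PS and N category are not among them.

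Both are nevertheless collected. Section 9.1.1, under "Information obtained before enrollment (entered in the enrollment form"), lists "ECOG performance status scale: PS (0, 1") and "TNM staging: T(1, 2, 3, 4a, 4b), N(0, 1, 2, 3), M(0"). Section 5.1 admits PS 0 and PS 1. The staging table in section 4.2 shows that a stage group does not fix N. One row reads "Stage III | T3 | N0, N1 | M0"; Stage IVA takes T1-T3 with N2 together with T4a with N0 to N2; Stage IVB takes T4b with any N together with N3 with any T.

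The planning target in section 12.1 is "two-sided α of 0.05, and statistical power of 80"%.

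**The concern.** In a proportional hazards analysis, leaving out a prognostic covariate pulls the estimated hazard ratio toward 1 and costs some power, even when the arms are balanced on it. Minimization does not control PS or N directly, so chance imbalance in either would also go uncorrected in the planned test. Both are pre-randomization values that the sites already enter, so using them needs no extra data.

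What is at stake is precision, not validity. In an open-label trial, an adjusted analysis is also more credible if it is fixed in advance than if it is added after the data are seen.

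**Working it through.** **1. The protocol's own figure.** Inputs from section 12.1: control 3-year DFS 50%, hazard ratio 0.7, 3 years of enrollment plus 3 years of follow-up, two-sided 0.05, power 80%. With exponential DFS:

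- Hazards: λ(UFT) = ln 2 / 3 = 0.231 per year; λ(TS-1) = 0.7 × 0.231 = 0.162. The TS-1 3-year rate is 0.5^0.7 = 0.616, which matches the stated 61.6%.
- Event probability with uniform accrual: 1 − (e^(−3λ) − e^(−6λ)) / (3λ) = 0.639 (UFT) and 0.512 (TS-1); mean 0.576.
- Schoenfeld: 4 × (1.960 + 0.842)² / (ln 0.7)² gives 247 events, or 247 / 0.5758 / 2 = 214.5 per arm. The Freedman formula gives 253 events and 219.7 per arm. The exponential log-hazard-ratio variance gives 216.9.

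The stated 216 per arm reproduces. With 500 subjects, 500 × 0.5758 = 288 events are expected, and the Schoenfeld power is 85.7%.

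**2. How thin the planned strata are.** 5 primary sites × 3 stage groups × 2 therapy types = up to 30 cells. If PS and N (N0, N1, N2-3) became further strata, Stage III would have 2 N levels and IVA and IVB 3 each, so 5 × 2 × (2 + 3 + 3) × 2 = 160 possible cells. That averages 288 / 160 = 1.8 events per cell. PS and N therefore belong in the model as covariates.

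**3. Effect of adding PS and N as covariates.** Simulation of 500 subjects, 3,000 runs per row. The overall 3-year DFS rates were held at 50% and 61.6% in every row, and all 30 strata were kept. Assumptions not found in the protocol:

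- PS 1 in 30% of subjects.
- Higher N within stage in 45%, 65% and 60% of Stage III, IVA and IVB.
- Stage mix 35/58/7%, and a hazard ratio of 1.3 per stage level.
- Therapy mix 65/35%.
- An assumed primary-site mix with modest site effects.

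| Assumed prognostic HR: PS / higher N | Mean events | Power, planned stratified log-rank | Power, stratified Cox + PS + N | Change (points) |
| --- | --- | --- | --- | --- |
| 1.0 / 1.0 | 286 | 82.7% | 82.5% | −0.2 |
| 1.3 / 1.3 | 286 | 81.4% | 82.0% | +0.6 |
| 1.5 / 1.5 | 284 | 82.5% | 84.2% | +1.7 |
| 2.0 / 1.5 | 283 | 81.6% | 85.7% | +4.1 |
| 2.0 / 2.0 | 281 | 81.5% | 86.2% | +4.7 |

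The Monte Carlo standard error of each power is √(0.82 × 0.18 / 3000) = 0.7 points. A stratified Cox model without PS and N gave 81.3% to 82.6%, so the gain comes from the covariates and not from replacing the log-rank test with a Cox model. In events, the last row corresponds to ((1.089 + 1.960) / (0.896 + 1.960))² = 1.14, or about 14% more events.

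A second simulation with the same overall rates and strata put the planned test at about 84% to 85%. The change was roughly 0 at hazard ratios of 1.0 to 1.3, +1 at 1.5, and +3 to +4 with PS at 2.0.

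**4. Coding of N.** A split of N0-1 against N2-3 is constant in Stage III, where only N0 and N1 occur. Keeping N0, N1 and N2-3 apart uses the information in all three stage groups. The simulation used a two-level marker of higher against lower N within stage, so its figures indicate the order of size for this coding and are not exact.

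**The case against.** The strongest reply is that nothing here is wrong. A log-rank test stratified by the minimization factors is valid and matches the design, and further adjustment is an optional efficiency choice. Stage is built from T and N, so part of the information in N is already used. Within IVA every N0-1 subject is T4a, and within IVB every N0-1 subject is T4b, so inside those groups higher N is set against higher T and the N effect may be small. PS is already restricted to 0 or 1. No section gives the prevalence or prognostic strength of either variable, so every gain above zero is an assumption. All of this stands, and it limits the point to a modest improvement.

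Two stronger readings are tempting and are not supported.

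- **The trial is underpowered without adjustment.** If 0.7 is taken as the hazard ratio conditional on PS and N, and primary site is left out of the model, unadjusted power falls to 79.5% at prognostic hazard ratios of 2.0 (83.5% adjusted). But section 12.1 ties 0.7 to overall rates of 50% and 61.6%, and a model without primary site is not the planned test. With those rates and all strata kept, the planned test stays above 80% in every scenario.
- **The protocol rules out covariates for the hazard ratio.** Section 12.3.1 names a Cox model and is silent on its covariates. The statistical analysis plan, which is not at hand, may list them. The point is firm only for the test, which the protocol does fix.

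**Conclusion.** The point holds as a low-cost improvement, not as an error. The test in section 12.3.1 is valid and meets its power target, but it passes over two baseline variables that are on the enrollment form before randomization and vary within the strata.

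The expected gain is about 0 points of power if PS and N are weakly prognostic (hazard ratio up to 1.3), 1 to 2 points at 1.5, and 3 to 5 points at 2.0. If they are not prognostic, the loss is within simulation error. The ranges rest on assumed covariate effects, prevalences and case mix, on exponential DFS and on no dropout. A reader might infer that power is certain to be gained; the documents do not support that, because they give no prognostic strength for either variable.

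**What to change.** In section 12.3.1, prespecify that the DFS treatment effect, both test and hazard ratio, comes from a Cox model that:

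- is stratified by primary site, stage and type of curative therapy, as now planned;
- has PS (0, 1) and N category (N0, N1, N2-3) as covariates, not as extra strata;
- takes both values as recorded on the enrollment form.

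Report the stratified log-rank test alongside it, and use the same model for RFS and OS.

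The cost is a short amendment to one section, with no new data or visits. The one downside is that the hazard ratio becomes a covariate-adjusted effect and must be labelled so, since it need not equal the ratio implied by the overall 50% and 61.6% rates.
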